**Fig. 5 Fig5:**
[figure not shown]
Mediation analysis. Key: RT = Respiratory Therapist, NIV = Noninvasive Ventilation

##### Power and sample size for aim 2

For aim 2 analyses, power was assessed for educational mode impact on job autonomy for respiratory RT measured by Aaron’s Job Autonomy Survey (AJAS), and team functionality measured by the ACE-15 tool. Estimating sample size to achieve 80% power, using a type I error rate of 0.05, a sample of 10 RT’s per hospital, will allow us to detect a moderate (Cohen’s *d* = .4) difference in AJAS at a 1-year post-intervention. This is accounting for clustering on hospital with intraclass correlation (ICC) in the range of .10–.20. Based upon data from local area hospitals, we estimate staffing of 8–10 RTs per 100 beds. For a few smaller hospitals, we will hope to include all RTs and may fall short of 10. Similarly, for the ACE-15, a sample size of 21 clinicians (7 each of RTs, RNs, and MDs) will achieve 80% power to detect a moderate effect size difference, accounting for clustering within hospitals, with ICC in the range of .10–.20 [50].

#### Specific aim 3

To evaluate the acceptability and feasibility of the IPE and OLE strategies and to inform further refinement of the strategies.

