##### Participants and settings

We will select a random sample of 10 RTs for the RT survey and 21 providers (7 from each discipline) for team functionality and organizational readiness for change surveys. A waiver of consent will be sent to all potential participants via email, the survey link will be included at the end of the email. To maximize participation, we will provide $25 incentives to participants.

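### Aim 2 power statement: 10 RTs per hospital do not give 80% power for d = 0.4 in AJAS at the stated ICC of .10–.20; the detectable d is about 0.58–0.70

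*Protocol article*

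**What the plan says.** All of this is in the protocol article.

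- **Power and sample size for aim 2, AJAS.** The target is 80% power, "using a type I error rate of 0.05, a sample of 10 RT’s per hospital", for a moderate effect given as Cohen's d = .4, described as a "difference in AJAS at a 1-year post-intervention". The next sentence reads "This is accounting for clustering on hospital with intraclass correlation (ICC) in the range of" .10–.20. The section concedes that a few smaller hospitals may supply fewer than 10 RTs.
- **Same section, ACE-15.** "a sample size of 21 clinicians (7 each of RTs, RNs, and MDs) will achieve 80% power to detect a moderate effect size difference", again with clustering said to be accounted for at ICC .10–.20. No numeric effect is attached to this sentence.
- **Aim 2, Participants and settings.** "We will select a random sample of 10 RTs for the RT survey and 21 providers" for the other surveys.
- **Power and sample size for aim 1.** The trial has 20 hospitals, 10 in each arm.
- **Aim 2, Statistical analysis.** The effect of the intervention on each mediator is estimated in multi-level models clustered on hospital. Adjustment for hospital and practitioner characteristics is mentioned. Adjustment for the baseline survey score is not.

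**The concern.** Hospitals are randomised, so RTs within a hospital are not independent. An ICC of .10–.20 with 10 RTs per hospital roughly doubles or triples the variance of the arm comparison. Yet d = 0.4 at 80% power is almost exactly what 100 independent RTs per arm would give. The stated d and the stated ICC range therefore cannot both hold at this sample size.

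The arm effect on RT autonomy and on team functionality is the first step of the mediation analysis, and mediation forms part of the central hypothesis set out at the end of the Background. If the stated power is too high, readers will give an inconclusive mediator comparison more weight than the design can bear.

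**Working it through.** **Inputs.** Hospitals per arm k = 10 (Aim 1 power section). RTs per hospital m = 10 and clinicians per hospital m = 21 (Aim 2 sections). Type I error 0.05, power 80%, ICC .10–.20 (Aim 2 power section). Sidedness is not stated; two-sided is assumed and one-sided is also tried.

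**Formulas.**
- Design effect DE = 1 + (m − 1) × ICC; effective size per arm n_eff = k × m / DE.
- Normal approximation: detectable d = (1.96 + 0.84) × √(2/n_eff); power = Φ(d × √(n_eff/2) − 1.96).
- Small-sample version: noncentral t with 2k − 2 = 18 df, which matches a comparison of 10 against 10 hospitals.

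**The plan's figure first.** With ICC = 0, n_eff = 100. Detectable d = 2.80 × √(2/100) = 0.396, and power at 0.4 is Φ(0.4 × √50 − 1.96) = Φ(0.87) = 80.7%. Without clustering, d = 0.4 needs 99 per arm. The stated figure is reproduced at ICC = 0.

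**AJAS, m = 10**

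| | ICC .10 | ICC .20 |
|---|---|---|
| DE | 1 + 9 × .10 = 1.9 | 1 + 9 × .20 = 2.8 |
| n_eff per arm | 100/1.9 = 52.6 | 100/2.8 = 35.7 |
| Power at d = 0.4, normal | Φ(0.09) = 54% | Φ(−0.27) = 39% |
| Power at d = 0.4, t with 18 df | 49% | 36% |
| Detectable d, normal | 2.80 × √(2/52.6) = 0.55 | 2.80 × √(2/35.7) = 0.66 |
| Detectable d, t with 18 df | 0.58 | 0.70 |

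With 8 RTs per hospital the detectable d rises to 0.61–0.73 (18 df).

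**ACE-15, m = 21 (210 per arm)**

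| | ICC .10 | ICC .20 |
|---|---|---|
| DE | 3.0 | 5.0 |
| n_eff per arm | 70 | 42 |
| Detectable d, normal / 18 df | 0.47 / 0.50 | 0.61 / 0.65 |
| Power at d = 0.4, normal / 18 df | 66% / 61% | 45% / 41% |
| Power at d = 0.5, normal / 18 df | 84% / 80% | 63% / 58% |

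**Readings that might rescue the AJAS claim**
- *One-sided 0.05:* power at d = 0.4 is 66% to 52% (normal) or 63% to 49% (18 df).
- *20 hospitals per arm, against the Aim 1 section:* 83% at ICC .10 but 67% at ICC .20 (normal), so the range is not covered.
- *Hospitals needed for d = 0.4:* 19–20 per arm at ICC .10 and 28–29 at ICC .20.
- *Baseline adjustment:* the share of variance to be removed is 1 − (0.4 / detectable d)². At ICC .10 this is 46% (normal) to 52% (18 df); at ICC .20 it is 64% to 67%. The corresponding baseline correlations are about 0.68–0.72 and 0.80–0.82. No such assumption is stated.

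**The case against.** **The calculation is not shown.** A reader might infer that the design effect was simply forgotten. The match at ICC = 0 (99 needed, 100 available) makes that likely, but nothing documents it. The match also belongs to an individual-level calculation: with 18 df the ICC = 0 value is 0.419. Like for like, the contrast is 0.396 against 0.55–0.66 by the normal approximation. This limits the diagnosis. It does not restore the claim, which fails under either convention.

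**ACE-15 is a different case.** It is tempting to say this claim fails in the same way. The document does not support that. Without clustering, 210 per arm would detect d = 0.273, so the same explanation does not fit. The .4 in brackets belongs to the AJAS sentence; for ACE-15 only the word moderate is given. If it means 0.5, the claim about holds at ICC .10 and fails towards .20.

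**More surveys per hospital.** A reader might conclude that no number of extra surveys could reach d = 0.4. With unlimited clinicians per hospital the detectable d tends to 2.80 × √(2 × ICC/10). That is 0.396 at ICC .10 (0.419 with 18 df) and 0.56 at ICC .20 (0.59 with 18 df). The conclusion is firm at .20 but depends on the convention at .10.

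**Importance.** The Abstract describes Aim 2 as exploratory, the 20 hospitals are set by Aim 1, and the power statement concerns the arm effect on each mediator, not the indirect effect. Nothing in the article says that a null mediator result would be taken as evidence against mediation. This stands and lowers the severity.

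**Condensation.** The full protocol may hold variance assumptions that the article omits. But this is an explicit numeric claim with its ICC range attached, and as printed it describes a difference at 1 year with no baseline-score adjustment.

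**Conclusion.** The AJAS power statement is wrong as written. At the stated ICC range the design has about 36% to 54% power at d = 0.4, not 80%, and it detects d of 0.55–0.66 (normal) or 0.58–0.70 (18 df). The assumptions are two-sided 0.05, 10 hospitals per arm, a full 10 RTs in each, and no baseline adjustment. Small hospitals would make the figures slightly worse.

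For ACE-15 the finding is narrower. The effect is unquantified, d = 0.4 is not reached anywhere in the ICC range, and d = 0.5 is reached only near its lower end.

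Severity is should-fix. The error concerns a secondary aim and leaves the primary outcome and the number of hospitals untouched.

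**What to change.** 1. In Power and sample size for aim 2, restate the detectable effects at 80% power over ICC .10–.20 as about 0.58–0.70 for AJAS and 0.50–0.65 for team functionality (two-sided 0.05, 10 hospitals per arm, 18 df).
2. Give the numeric effect that moderate stands for in the ACE-15 sentence, and state the sidedness of the test.
3. Optionally, adjust the 1-year comparison for the baseline survey and state the variance reduction assumed. Reaching d = 0.4 for AJAS would need roughly 46–52% (ICC .10) to 64–67% (ICC .20) of the variance removed. The article does not say whether the same clinicians are followed or a new sample is drawn each time. Individual baseline scores can be used only in the first case; in the second, adjustment would be for the hospital mean.

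Items 1 and 2 cost only wording and less favourable printed figures. Item 3 uses the baseline survey that is already planned. No extra hospitals or clinicians are required.

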##### Study design

To achieve this aim, we will perform a qualitative study using semi-structured interviews with providers to assess relative importance of various barriers and determinants on the implementation of the two strategies.

##### Participants and settings

We will recruit a random sample of nurses, physicians, and RTs. As it is typical in qualitative research, the total sample is not fixed; depending of the size of the program, we will select 2–4 individuals from each profession in each hospital and expect to enroll approximately 40–50 providers enabling us to reach thematic saturation. Potential participants will be contacted via email by the study research assistant and invited to conduct an interview. A waiver of consent will be included in the body of the email prior to the contact information for the interview. Those who are interested in participating will be contacted by telephone to arrange an interview time over the telephone. To maximize participation, we will provide $50 incentives and schedule sessions at a time convenient to the participants.

##### Data collection

We anticipate that interviews will last approximately 30 min. All interviews will be audio recorded and transcribed verbatim. The interview team will consist of one research associate who will be trained by the investigator. The focus of the interviews will be to explore the implementation process—the acceptability and feasibility of the educational training strategies, participation in the training sessions, barriers to participation, adaptation made to the training sessions, and how the NIV protocol was incorporated into the clinical workflow.

##### Expected outcomes

This qualitative analysis will allow us to gain a broader perspective on the process of implementation from the perspective of the participants. We expect to understand and identify barriers and facilitators and their relative importance for this implementation strategy to be the most successful. The knowledge gained from this aim will be important for further application and refinement of IPE for other therapies/interventions directed to the critically ill patients.

##### Data analysis

Transcripts will be reviewed by the interviewer for accuracy. Qualitative data management and analysis software (NVivo) will be used to organize and code the data [51]. The nature of the interviewee role and the setting in which they work will be summarized and reported by location. We will use directed qualitative content methods to analyze interview content, beginning with a coding framework based on our prior work [52, 53]. Coding will occur concurrently with the interviews to ensure that the interview guide is eliciting data related to the domains of interest. Two team members will be primarily responsible for coding and will be supervised by one co-investigator proficient in qualitative analysis. The first 2 interviews will be read by each researcher with the goal of agreeing on the use of the domains and or constructs. This codebook will be used for all interviews going forward, with the team meeting periodically to discuss the emergence of any new codes or to clarify the relevance of domains and constructs to the text. Each transcript will be coded twice, once by each researcher. Discrepancies will be discussed until consensus is reached. Through regular investigators meetings, we will generate overarching themes.

### Economic evaluation

The investigation will collect the following information to calculate the costs to initiate the intervention: (1) cost of the training of the COPD-NIV team in the IPE arm of the study and inclusive of salary/fringe costs of the implementation specialists travel to the one day training session, (2) cost of webinars inclusive of speaker costs and video recording costs, and (3) cost of the continuing educational credits provided to the clinicians attending the IPE sessions at their hospitals and to the COPD-NIV team for their attendance of the 1-day session and for teaching the COPD-NIV-IPE course at their hospital.

### Dissemination

We propose the following strategies for dissemination: (1) after study completion, we will host webinars to share the results with the participant hospitals; (2) we will develop a one-page information sheet with the results and conclusion of the study and distribute it on the Premier Inc. website; (3) we will develop a toolkit and implementation manual with step-by-step guidance to help other institutions implement the IPE strategy; (4) publications and presentations at national and international respiratory and D&I conferences; and (5) we will work with Society of Hospital Medicine and COPD foundation to share the finding of the study to their members.

Table 3 present the proposed timeline for the study.

**Table 3 Tab3:**
[figure not shown]
Proposed timeline

### Potential limitation and rational for key decisions

#### Why study only education?

We have carefully considered other implementation strategies such as audit and feedback, which is an electronic medical records decision support tool and academic detailing. When mapping the barriers within ERIC compilation of implementation strategies, we found that IPE covered several of identified barriers. Additionally, we were concern that using multiple strategies would complicate our attempt to understand the educational intervention impact. Interprofessional care is essential to the management of seriously ill patients and in the absence of robust studies to determine if IPE indeed impact patient outcomes, it is critical to be able to assess it in randomized controlled trial.

#### Why limit the trial to Premier hospitals?

For this pragmatic clinical trial, we need to be able to calculate hospitals’ NIV rates and identify low performing hospitals to be able to invite them to participate in the trial and determine the rates after the implementation period. Our intention was to have these rates calculated directly from the administrative or electronic data without a need for data collection. We did not come across any other database which provides the needs for this trial.

Still, if the trial shows that IPE is effective in improving the NIV rates, individual hospitals will be able to calculate their own rates and decide if they want to implement the IPE strategy.

## Discussion

This study will be among the first to carefully test the impact of IPE in the inpatient setting. Over the last 20 years, there have been increasing interest in linking IPE with interprofessional collaboration and team-based care [26, 54]; however, only recently have researchers begun to look beyond the classroom and beyond learning outcomes on such issues as patient safety, patient and provider satisfaction or quality, and cost of care. Consequently, the 2015 Institute of Medicine Report “Measuring the impact of interprofessional education on collaborative practice and patient outcomes” questions calls for purposeful, well-designed, robust studies to understand the link between IPE and patient and health systems outcomes [55]. Therefore, our study will add to the evidence by comparing an IPE strategy specifically designed to improve team functionality for NIV delivery in a pragmatic randomized controlled trial against an active, realistic control.

## Data Availability

Not applicable for this section

## Abbreviations

COPD: Chronic obstructive pulmonary disease
IMV: Invasive ventilation
NIV: Noninvasive ventilation
RT: Respiratory therapist
OLE: Online education
IPE: Interprofessional education
ARF: Acute respiratory failure
TDF: Theoretical domain framework
ERIC: Expert Recommendations for Implementing Change
COPD-NIV Team: Chronic Obstructive Pulmonary Disease-Noninvasive Ventilation Team
IPEC: Interprofessional Education Collaborative
RS: Risk standardized
ICD-10-CM codes: International Classification of Diseases, 10^th^ Revision, Clinical Modification codes
ICD: International Classification of Diseases
ICD-9-CM: International Classification of Diseases, 9^th^ Revision, Clinical Modification
GEE models: Generalized Estimating Equations model
ORIC: Organizational readiness for implementing change
IOM: Institute of Medicine
ACE-15: Assessment of Collaborative Environments
SEM: Structural equation model
AJAS: Aaron’s Job Autonomy Survey
ICC: Intraclass correlation
COPD-NIV-IPE: Chronic Obstructive Pulmonary Disease- Noninvasive Ventilation-Interprofessional Education
D&I Conferences: Dissemination and Implementation Conferences
